## Abstract

**Background:**

Groin pain is a frequent complaint in surgical practice with an inguinal hernia being at the top of the differential diagnosis. The majority of inguinal hernias can be diagnosed clinically. However, patients with groin pain without signs of an inguinal hernia on anamnesis or physical examination provide a diagnostic challenge. If ultrasonography shows a hernia that could not be detected clinically, this entity is called a clinically occult hernia. It is debatable if this radiological hernia is the cause of complaints in all patients with inguinal pain.

The objective of this study is to assess whether watchful waiting is non-inferior to endoscopic totally extraperitoneal (TEP) inguinal repair in patients with a clinically occult inguinal hernia.

**Methods:**

The EFFECT study is a multicenter non-blinded randomized controlled non-inferiority trial. Adult patients with unilateral groin pain and a clinically occult inguinal hernia are eligible to participate in this study. A total of 160 participants will be included and randomized to TEP inguinal hernia repair or a watchful waiting approach. The primary outcome of this study is pain reduction 3 months after treatment, measured by the Numeric Rating Scale (NRS). Secondary outcomes are quality of life, cost-effectiveness, patient satisfaction and crossover rate. Eight surgical centers will take part in the study. Participants will be followed-up for 1 year.

**Discussion:**

This is the first large randomized controlled trial comparing treatments for patients with groin pain and a clinically occult inguinal hernia. To date, there are no interventional studies on the effect of surgery or a watchful waiting approach in terms of pain or quality of life in this subset of patients. A trial comparing the outcomes of the two approaches in patients with a clinically occult inguinal hernia is urgently needed to provide data facilitating the choice between the two treatment options. If watchful waiting is not inferior to surgical repair, costs of surgical repair may be saved.

**Trial registration:**

The study protocol (NL61730.100.17) is approved by the Medical Ethics Committee (MEC-U) of the Diakonessenhuis, Utrecht, The Netherlands. The study was registered at the Netherlands Trial Registry (NTR6835) registered on November 13, 2017.

**Electronic supplementary material:**

The online version of this article (10.1186/s13063-018-2711-7) contains supplementary material, which is available to authorized users.

## Background

Groin pain is a frequent complaint in surgical practice that encompasses a large number of possible etiologies. A well-known cause of groin pain is an inguinal hernia. Elective inguinal hernia correction is the most commonly performed operation worldwide with an estimated 30.000 procedures in the Netherlands annually [1].

In the majority of cases, an inguinal hernia can be diagnosed clinically. A classical hernia presents as a reducible groin swelling with a positive cough impulse (Valsalva manoeuvre), with or without the presence of discomfort. However, patients with groin pain without signs of an inguinal hernia on anamnesis or physical examination provide a diagnostic challenge.

For patients with groin pain in whom no swelling can be identified, current guidelines advise ultrasonography of the groin, followed by MRI if ultrasonography is inconclusive [2, 3]. When additional imaging shows a hernia that could not be detected clinically, this entity is called a clinically occult hernia. The current guidelines do not provide a specific therapeutic approach for this type of hernias, and for unclear reasons the radiologic presence of a clinically occult inguinal hernia often leads to surgical intervention [2, 3].

However, it is debatable if in all cases a symptomatic inguinal hernia truly exists or whether the hernia on additional imaging is an incidental finding with an alternative cause for the pain complaints. The radiologic finding might even be false-positive in some cases. Considering this, it is likely that not in all patients with a clinically occult hernia a surgical procedure is justified, and it is possible that (chronic) pain complaints persist or increase after surgery. This consideration is important for adequate patient information and avoidance of unnecessary surgical interventions.

The incidence of groin pain in combination with a clinically occult inguinal hernia is not well described in literature. A prospectively registered database kept in the Hernia Clinic of the Diakonessenhuis (Diakonessenhuis Utrecht/Zeist, The Netherlands) shows inguinal pain without symptoms of an inguinal hernia on physical examination or anamnesis but presence of an inguinal hernia on ultrasonography in 9.5% of patients.

Up till now, there are no studies performed specifically focusing on the course of pain and quality of life after correction of a (clinically) occult inguinal hernia or a watchful waiting approach. A trial comparing the outcomes of the two approaches in patients with a clinically occult inguinal hernia is urgently needed.

## Methods

### Objective

The objective of this study is to assess if watchful waiting is non-inferior to endoscopic totally extraperitoneal (TEP) inguinal repair in patients with a clinically occult inguinal hernia.

### Study design

The EFFECT trial is designed as a non-blinded, randomized controlled non-inferiority trial comparing surgical treatment by TEP repair to watchful waiting in patients with a clinically occult inguinal hernia. This study is conducted in accordance with the principles of the Declaration of Helsinki and Good Clinical Practice guidelines. The independent ethics committee of the Diakonessenhuis Utrecht (MEC-U) has approved this study protocol (protocol number NL61730.100.17). Eight Dutch centers participate in this study: Diakonessenhuis Utrecht/Zeist, Meander Medical Center Amersfoort, Onze Lieve Vrouwe Gasthuis (OLVG) Amsterdam, Maasstad Hospital Rotterdam, Maxima Medical Center (MMC) Veldhoven, Elkerliek Hospital Helmond, Rode Kruis Hospital (RKZ) Beverwijk and Treant Care Group Hoogeveen.

Patient recruitment started on December 29, 2017. Written informed consent will be obtained from all participants by the study coordinator. Inclusion will take up to a maximum of 2.5 years and participants will be followed up for 1 year in total. The total duration of the study will be 3.5 years. All study participants will be asked to fill out written questionnaires at different time points (baseline, 1.5, 3, 6 and 12 months following treatment) and will be scheduled for physical examination by experienced hernia surgeons at two additional time points at the surgical outpatient clinic for the purpose of this study Participants can withdraw from the study at any time, for any reason.

Randomization, collection and storage of study data will take place through a uniform electronic case report form (eCRF).

A SPIRIT figure and checklist for this study protocol are provided in Fig. 1 and Additional file 1, respectively.

**Fig. 1 Fig1:**
[figure not shown]
Content for the schedule of enrolment, interventions and assessments according to the SPIRIT statement. *ASA* American Society of Anesthesiologists, *BMI* body mass index, *MRI* magnetic resonance imaging, *TEP* totally extraperitoneal, *Findings upon operation in case of randomization to totally extraperitoneal (TEP) hernia repair. **Patient diary regarding physiotherapy and use of painkillers

### Participants

Adult patients with groin pain and a clinically occult inguinal hernia are eligible to participate in this study*.*

All patients presenting to the outpatient clinics of participating centers are physically examined by experienced hernia surgeons and screened for trial eligibility (Fig. 2). Patients will be informed and included at the surgical outpatient department at one of the participating centers.

**Fig. 2 Fig2:**
[figure not shown]
Study flow chart. *TEP* totally extraperitoneal

Each subject must meet the following inclusion criteria:Age ≥ 18 yearsUnilateral groin painNo features of an inguinal hernia on anamnesis (no visible or palpable groin swelling)No features of an inguinal hernia on physical examination (no visible or palpable groin swelling and a negative Valsalva manoeuvre)Radiological diagnosis of an inguinal hernia on ultrasonography

A potential subject who meets any of the following criteria will be excluded from participation:Previous inguinal hernia on the symptomatic sidePrevious surgery in inguinal region of the symptomatic sideBody mass index (BMI) ≥ 40American Society of Anesthesiologists (ASA) classification > IIIFactors that complicate follow-up by means of questionnaires (e.g. language barrier, psychiatric disorders)Unwillingness to undergo surgery

### Randomization

After informed consent is obtained, the study coordinator will directly randomize patients to either TEP repair or a watchful waiting approach by means of an online random treatment generator, stratified by center.

The surgeon, patient and coordinating researcher are not blinded for the allocated treatment.

### Baseline assessment

At baseline, all participants are asked to fill out electronic questionnaires. Also, all participants will undergo X-ray and magnetic resonance imaging (MRI) of the pelvis, to be able to assess baseline comparability of the groups in a later stage. The surgeon will be blinded to the outcomes of these investigations and they do not influence treatment. Only in rare severe cases (e.g. a tumor or fracture) radiologists are instructed to contact the treating physician.

### Intervention

Patients will be randomized to TEP inguinal hernia repair or a watchful waiting approach.

#### TEP inguinal hernia repair

The patients randomized to an operative treatment will undergo endoscopic totally extraperitoneal (TEP) inguinal hernia repair. This procedure will be standardized according to current guidelines in all participating centers [2, 3].

A preperitoneal synthetic mesh will be placed in a standardized manner. Perioperative findings (presence of an inguinal hernia, classification of inguinal hernia according to the European Hernia Society (EHS) hernia classification, presence of a lipoma) and perioperative complications are recorded in the operation chart [2, 3].

#### Operative procedure

After induction of general anaesthesia, a sub-umbilical incision is made. The anterior rectus sheath is divided transversely to expose the rectus muscle, which is retracted laterally. A 10 mm trocart is inserted into the preperitoneal space after which the preperitoneal space is created digitally (or with a balloon) and insufflated. A 5 mm trocart is placed at midline between umbilicus and symphysis, after which the pubic bone and cavum Retzii are dissected. Below the level of the epigastric vessels lateral dissection takes place, and a second 5 mm trocart is placed laterally. (Another option is placement of the second 5 mm trocart in the midline, below the first 5 mm trocart). A possible lateral hernia sac is dissected with identification of the vas deferens and vessels. A possible medial of femoral hernia is reduced. The peritoneum is dissected cranially. Possible lipomas are identified and reduced or resected. A synthetic mesh is introduced and positioned against the anterior abdominal wall, covering the internal ring, the femoral canal and the medial space. Next, under endoscopic sight the preperitoneal space is desufflated, and all trocarts are removed. The rectus sheath is closed with vicryl, the dermis is closed with monocryl.

#### Postoperative care

Patients are discharged at the day of surgery, unless complications prohibit early discharge.

Participants are advised to avoid strenuous physical activity during the first postoperative week.

#### Surgical quality control

A selected number of trained surgeons will perform TEP hernia repair. Hereby, we maintain quality of the operations and minimize differences in success rates. Surgeons in the participating centers have completed their learning curve and are sufficiently experienced (> 250 procedures per individual surgeon) in TEP inguinal hernia repair.

#### Watchful waiting

Patients in the watchful waiting study arm will be treated with rest, pain killers and optional physical- and/or physiotherapy. It is expected that the patients in this group will present with a variety of complaints and will not experience the same (intensity of) complaints, therefore we cannot standardize the treatment in this study arm. Intensity and frequency of this treatment will depend on the amount of complaints the individual patient is experiencing and is expected to differ between patients. The decision to offer physical- and/or physiotherapy will be in the hands of the treating physician, who will decide if he or she suspects the kind of complaints where physical- and/or physiotherapy will be of help.

### Outcomes

The primary outcome will be pain reduction after 3 months, measured at rest and during physical activity. The first pain score is obtained at baseline. The first three questions of the validated EuraHS Quality of Life (EuraHS-QoL) reflect intensity of pain on an 11-point numeric rating scale (NRS) (0–10 where 0 reflects “no pain” and 10 reflects “the worst possible pain”) [4]. Patients rank the intensity of their pain on this scale at rest (specified as lying down) and during physical activity (defined as walking, cycling or practicing sports). The third question is the amount of pain felt during the last week, so insight is also provided in the most recent pain the patient experienced. Follow-up pain levels are determined at three additional time points (1.5, 6 and 12 months following treatment) as secondary outcome parameters.

Secondary outcomes include quality of life, cost-effectiveness, patient satisfaction and crossover rate. Quality of life will be assessed by the validated EuraHS-QoL and Euro Quality of Life-5D-5 L (EQ5D-5 L) questionnaires at baseline, and 1.5, 3, 6 and 12 months postoperatively [5].

Cost-effectiveness will be based on all resources used within and outside the hospital and productivity loss for both groups of patients. The acquired data will consist of all health care professional visits, hospitalizations, imaging, biochemical investigations and surgery. Health care use will be monitored through the medical consumption questionnaire (MCQ), a generic instrument for measuring health care use and calculating medical costs, at 1.5,3, 6 and 12 months after treatment [6]. Participants in both treatment groups will be given a patient diary where the use of painkillers and (optional) treatment with physical- and/or physiotherapy will be registered the first 6 weeks after treatment. Productivity will be measured through the productivity cost questionnaire (PCQ), a standardized instrument for measuring and valuing productivity losses, at 1.5,3,6 and 12 months after treatment [7]. We aim to calculate total costs per patient in every group. We aim to calculate cost-effectiveness ratios to indicate the total costs per additional unit of effect, cost per quality-adjusted life year (QALY).

Patient satisfaction will be measured at 3 and 12 months after treatment. The measuring instrument for the outcome parameter patient satisfaction is a self-designed 11-point scale ranging from 0 (“no satisfaction”) to 10 (“total satisfaction”).

The crossover rate will reflect the percentage of patients initially assigned to the watchful waiting group that crosses over to surgical treatment.

Other study parameters include baseline characteristics (gender, age, ASA classification, BMI, smoking, medication, side of complaints, duration of complaints, previous inguinal hernia on contralateral side), perioperative outcomes (presence of a hernia, hernia type, presence of lipoma, duration of surgery, conversion, complications) and postoperative complications. Also, the percentage of clinically occult hernias in the watchful waiting group that develop into clinically overt inguinal hernias will be assessed.

### Sample size calculation

The sample size determination is based on the assumption that a watchful waiting approach is non-inferior to a TEP inguinal hernia correction; from this assumption there is no expected difference between the difference scores of both groups. No consensus exists concerning a minimal clinically relevant difference on the NRS, though previously published literature describes a difference of one point [8]. We used three-quarters of a point (0.75) on the NRS scale as an equivalence margin, using the NRS as a continuous variable. Expected variance in the primary outcome was estimated from a prospectively collected database containing 919 patients at the Diakonessenhuis; a standard deviation of 2.3 was found for the difference scores, and a correlation of 0.8 was found between pretreatment pain and change in pain scores. To be able to detect an equivalence margin of 0.75 on change on the NRS scale between the groups, with a power of 90% and a one-sided alpha of 0.025, a sample size of 199 patients in each arm is required. Because we will correct for baseline pain intensity, an analysis of covariance (ANCOVA) correction was used, resulting in 72 patients per arm [9]. Taking a loss-to-follow-up of 10% into account, the total sample size should contain at least 160 patients with 80 patients per arm.

### Statistical analysis

#### Primary outcome measure

The primary outcome measure is the difference in pain intensity (NRS during rest/physical activity) 3 months following treatment compared to baseline. Difference scores of the NRS (posttest minus pretest) will be used in both treatment groups. The NRS score will be used as a continuous variable. For comparison of difference scores an ANCOVA will be used, in which the estimated difference in pain scores will be corrected for the pain intensity at baseline.

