#### Secondary/other study parameter(s)

Continuous secondary outcomes 3 months following treatment will be analyzed similarly to the primary outcome, with an ANCOVA on the difference scores correcting for baseline scores. Outcome measures at 1.5,3,6 and 12 months following treatment will be analyzed using linear mixed-effects models to adjust for repeated measurements within individuals. Contrasts will be used to investigate differences between the study arms at the post-treatment time points.

The primary analysis of outcome parameters is an intention-to-treat analysis. Primary and secondary outcomes 3 months after treatment will also be evaluated only for the patients who remained in the arm to which they were randomized (per protocol analysis).

Data will be analyzed by means of IBM SPSS Statistics version 23 or higher (IBM Corp, Armonk, NY, USA).

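### Centre is a stratification factor but is not in the stated ANCOVA; if outcomes differ between centres, the non-inferiority test will be somewhat conservative

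*Protocol article*

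**What the plan says.** Under Randomization, the Protocol article allocates patients "by means of an online random treatment generator, stratified by center". Under Study design it says "Eight Dutch centers participate in this study".

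Under Primary outcome measure, the analysis compares 3-month change in NRS pain by ANCOVA, and "the estimated difference in pain scores will be corrected for the pain intensity at baseline". Under Secondary/other study parameter(s), continuous outcomes at 3 months are handled in the same way, "with an ANCOVA on the difference scores correcting for baseline scores". The linear mixed models for the repeated time points are described only as allowing for correlation within individuals. Centre is named in none of these models.

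The Sample size calculation section uses a margin of 0.75 NRS points, a true difference of zero, an SD of 2.3 for the change scores, and a reduction for baseline correction. It mentions no centre effect and gives no between-centre variance.

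**The concern.** Stratifying by centre makes the arms nearly balanced within each centre. Differences between centres in average outcome then largely cancel out of the treatment comparison. A model without centre does not know this: it leaves the between-centre variance in the residual and reports a standard error larger than the true sampling error of the estimate.

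The trial has to show that watchful waiting is no more than 0.75 points worse, presumably by setting a confidence limit against that margin. An interval that is wider than necessary makes a true non-inferiority finding harder to reach. Some centre differences are plausible. The Watchful waiting section says that treatment in that arm cannot be standardised and leaves physiotherapy to the treating physician. Pain is also self-reported in an unblinded trial.

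**Working it through.** **Inputs from the Protocol article (Sample size calculation, Study design).** Margin 0.75; true difference 0; SD of change 2.3; correlation of baseline pain with change 0.8; power 90%; one-sided alpha 0.025; 72 analysed per arm; eight centres.

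**Assumed.** The ICC, meaning the share of residual variance that lies between centres. The documents give none, so a range is shown.

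**1. The plan's own figures.** Normal approximation: n = 2 × [2.3 × (1.960 + 1.282) / 0.75]² = 197.6, so 198 per arm; the t-based calculation gives the stated 199. Baseline correction: 199 × (1 − 0.8²) = 199 × 0.36 = 71.64, so 72. Loss to follow-up: 72 / 0.90 = 80 per arm, 160 in total. All stated figures reproduce, and none relies on centre adjustment.

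**2. The stated model.** Residual SD = 2.3 × √(1 − 0.64) = 1.38. SE = 1.38 × √(2/72) = 0.230. Residual df = 144 − 3 = 141, t = 1.977, half-width = 0.4547.

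**3. The model with centre.** Seven indicators leave 141 − 7 = 134 df, t = 1.978. SE_c = 0.230 × √(1 − ICC); half-width = 1.978 × SE_c; power from the noncentral t.

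**4. The stated model when centres differ.** The estimate varies with SE_c, but the model reports 0.230. Power ≈ Φ[(0.75 − 0.4547) / SE_c]. One-sided error ≈ 1 − Φ(1.960 × 0.230 / SE_c).

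| ICC (assumed) | SE_c | Half-width, baseline only | Half-width, with centre | Change | Power, baseline only | Power, with centre | One-sided error, baseline only |
|---|---|---|---|---|---|---|---|
| 0 | 0.230 | 0.4547 | 0.4549 | none | 90.0% | 89.9% | 0.025 |
| 0.02 | 0.228 | 0.4547 | 0.4503 | −1.0% | 90.3% | 90.5% | 0.024 |
| 0.05 | 0.224 | 0.4547 | 0.4434 | −2.5% | 90.6% | 91.3% | 0.022 |
| 0.10 | 0.218 | 0.4547 | 0.4316 | −5.1% | 91.2% | 92.7% | 0.019 |
| 0.20 | 0.206 | 0.4547 | 0.4069 | −10.5% | 92.4% | 95.2% | 0.014 |

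**5. Simulation check.** Eight equal centres of 18, permuted blocks of 4 or 6 (both assumed), 6000 runs per setting. Mean half-widths without and with centre were 0.455 and 0.456 at ICC 0, 0.454 and 0.445 at 0.05, and 0.453 and 0.433 at 0.10. Power was 89.6% and 89.5%, 90.4% and 91.0%, and 91.7% and 92.9%. The one-sided error of the baseline-only model was 0.029, 0.024 and 0.019. The Monte Carlo standard error is √(0.025 × 0.975 / 6000) ≈ 0.002, so these agree with the formulas within noise.

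**6. Sensitivity to the source of the SD.** The SD and correlation come from a database at one participating hospital, so 1.38 may be nearer a within-centre SD. Centre variance would then come on top. The baseline-only half-width becomes 0.4547 / √(1 − ICC), which is 0.467 at ICC 0.05 and 0.479 at 0.10. Power is Φ[(0.75 − 0.467) / 0.230] ≈ 89% and Φ[(0.75 − 0.479) / 0.230] ≈ 88%, against 89.9% with centre at either ICC. The conclusion and its order of size do not change.

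**The case against.** The strongest reply is that nothing here is quantified by the documents. A reader might infer that the planned interval is certainly too wide. The text does not support that: no between-centre variance is given, and at ICC 0 adding centre gains nothing. Repair is standardised across centres and done by surgeons with more than 250 procedures each, which points to small centre effects. The variation in watchful waiting is attributed mainly to individual patients. Any centre variation confined to that arm would be partly a treatment-by-centre interaction, which a centre main effect does not fully remove. All of this stands, and it makes the point conditional.

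A reader might also infer a raised risk of wrongly declaring non-inferiority. The reverse is true: the error is in the safe direction. Nor was the sample size built on a centre-adjusted model; it was built on baseline correction alone and agrees with the stated analysis. The confidence-interval rule is itself an inference from the margin and the one-sided alpha, as the article does not spell it out.

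Finally, this is a condensed article, and a full protocol or SAP may add centre. That is a fair reason not to criticise the mixed models, for which no covariates are listed at all. It is weaker for the ANCOVAs, where the article names both the model and its covariate. As written, they do not reflect the stratified design.

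**Conclusion.** The point holds in conditional form. The design stratifies by centre, and the stated primary and 3-month secondary ANCOVAs correct only for the baseline score. If centres differ in outcome, the stated analysis is conservative.

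For the primary outcome, at assumed ICCs from 0 to 0.10, the interval with centre is 0 to about 5% narrower, which is at most 0.023 NRS points on the half-width (0.4547 − 0.4316). The power gain is at most about 1.5 points. These figures assume 72 analysed per arm, a total residual SD of 1.38, near-balance within centres and a common treatment effect across centres; the simulation also assumes equal recruitment. Very small centres would make seven separate indicators less efficient, hence the pooling option in the fix.

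This is a free improvement in efficiency and consistency. It does not indicate an invalid test, an inflated false-claim risk or a faulty sample size.

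**What to change.** Under Primary outcome measure, state that the ANCOVA includes centre as well as baseline pain, either as a fixed effect with a pre-stated rule for pooling small centres, or as a random intercept. Carry the same wording into the 3-month ANCOVAs under Secondary/other study parameter(s). If the full protocol or SAP already does this, bring the article's text into line; if centre is left out on purpose, give the reason.

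The choice should be fixed before the data are seen. In an unblinded trial with a result near 0.75, adding centre later would look data-driven.

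The cost is one phrase and at most 7 of 141 residual degrees of freedom. At ICC 0 that moves the half-width from 0.4547 to 0.4549. The sample size need not change.
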